## Abstract

**Background:**

Traumatic brain injury (TBI) carries significant mortality and morbidity in civilian and military populations. Current treatment guidelines for TBI are primarily supportive, and no pharmacological agent exists to attenuate the progression of brain injury. Valproic Acid (VPA) has long been used to treat neurological disorders; however, recent work has demonstrated its potential as a neuroprotective agent. We have already demonstrated that VPA administration in swine models of TBI (with or without associated hemorrhage and polytrauma) significantly improves survival and neurological recovery and decreases brain lesion size compared to controls. This paper introduces a phase 2/3 clinical trial that is designed to evaluate the efficacy and safety of VPA administration in patients with TBI.

**Methods:**

In this randomized, double‐blind, placebo‐controlled, multicenter trial, patients with moderate to severe TBI (GCS 3–12) across nine level 1 trauma centers in the US will be randomized to receive either standard of care treatment and 250 mL of isotonic saline (control), or standard of care treatment and intravenous VPA at either 50 mg/kg (low‐dose VPA group), or 100 mg/kg (high‐dose VPA group). The primary endpoint of this clinical trial will be neurological status as measured by the Extended Glasgow Outcome Scale (GOS‐E) 3 months post‐TBI.

**Discussion:**

Our team has conducted multiple large animal studies that strongly support the cytoprotective effects of VPA treatment. The goal of this upcoming trial is to study the efficacy and safety of two doses of VPA in patients with moderate to severe TBI.

**Trial registration:**

ClinicalTrials.gov, https://clinicaltrials.gov/study/NCT07166393, September 3, 2025.

AbbreviationsAEadverse effectsaPTTactivated partial thromboplastin timeBMIbody mass indexc‐IRBcommon institutional review boardCDMRPcongressionally directed medical research programCTcomputed tomographyDCRdamage control resuscitationDLTdose‐limiting toxicitiesDMCdata monitoring committeeDRSdisability rating scoreDSMBdata safety monitoring boardEFICexception from informed consentFDAFood and Drug AdministrationGABAgamma‐aminobutyric acidGADglutamic acid decarboxylaseGCSGlasgow coma scoreGOS‐Eextended Glasgow outcome scoreHAThistone acetyltransferasesHDAChistone deacetylasesHDACihistone deacetylase inhibitorHPChemorrhagic progression of the contusionICAMintracellular adhesion moleculeICPintracranial pressureINRinternational normalized ratioITinformation technologyITTintent‐to‐treatIVintravenousK_2_EDTAdipotassium ethylenediaminetetraacetic acidLARlegally authorized representativesMICEmultiple imputation by chained equationsNSnormal salineNSSneurological severity scoreNUCATSNorthwestern University Clinical and Translational Sciences InstituteNUDACCNorthwestern University data analysis and coordinating centerNURIPSNorthwestern University research image processing systemPBMCperipheral blood mononuclear cellPDpharmacodynamicPFCprolonged field carePIprincipal investigatorPKpharmacokineticPODpost‐operative dayPTprothrombin times‐IRBsingle institutional review boardSRCsafety review committeeTBItraumatic brain injuryVIBRANTvalproic acid for traumatic brain injury trialVPAvalproic acid

## INTRODUCTION

1

Traumatic brain injury (TBI) is a major contributor to trauma‐related death and carries a significant long‐term morbidity burden. Nearly 2 million Americans suffer from new TBIs every year, and 50 million people worldwide are estimated to suffer from TBI annually, resulting in a global economic burden of $400 billion.^1^, ^2^ While this is important among civilian trauma patients, the prevalence and significance of this injury are particularly impactful among military service members. It has been established that TBI is a leading cause of battlefield mortality.^3^ Additionally, non‐fatal TBI is common in veterans, with more than 400,000 U.S. service members having suffered a TBI between the years of 2000 and 2022.^4^

Hemorrhage and TBI are the leading causes of death in the combat setting, where 87% of deaths occur before reaching a medical facility.^5^ Often, hemorrhagic shock and TBI are present together and in conjunction with other injurious mechanisms. The difficulty of treating TBI is underscored in these poly‐trauma patients, where different afflictions necessitate discrepant treatment goals. While TBI management guidelines recommend maintaining an elevated blood pressure to mitigate brain injury secondary to the primary insult, ongoing hemorrhage requires keeping blood pressure low.^6^, ^7^ While this scenario is challenging even in well‐equipped settings, the complexity of this situation is amplified in resource‐limited environments.

Current management guidelines for TBI are largely supportive, with no treatment options that specifically target the injured brain and improve neurologic and functional outcomes.^8^ Management of TBI patients—particularly those that present with other traumatic injuries—is resource‐intensive and requires team‐based, round‐the‐clock monitoring that is limited in austere military environments. While hospitals are typically well‐equipped to manage critically ill patients, military medicine can be marked by fewer personnel, equipment, and therapeutic options. The complexity and difficulty of treating TBI patients in military settings are expected to increase, with Department of Defense (DOD) predictions that future near‐peer conflicts will be marked by contested airspace hindering extrication to military treatment facilities.^9^ This change is anticipated to increase the time spent in prolonged field care (PFC) compared to past conflicts. Thus, there is a clear need to not only identify a safe and effective neuroprotective agent capable of mitigating underlying injurious processes of TBI, but one that can also be administered in austere environments. Such an agent could allow civilian and military providers alike to treat TBI while providing significant logistical benefits in the setting of PFC.

Over the past decade, our team has extensively investigated the role of valproic acid (VPA), a Food and Drug Administration (FDA)‐approved small molecule drug, as a potential treatment for TBI across numerous preclinical models. Between our translational models and confirmatory dose‐escalation models in humans, we have collected sufficient data on preclinical efficacy and clinical safety to justify a clinical trial aimed at evaluating VPA treatment in TBI patients. In this paper, we will discuss the proposed mechanism of VPA as a neuroprotective agent, discuss the relevant preclinical and clinical data supporting VPA as a potential treatment for TBI, and provide details of our upcoming randomized, placebo‐controlled, multi‐institutional clinical trial.

## RATIONALE FOR VALPROIC ACID TREATMENT

2

VPA has long been established as a treatment for a multitude of neurological and psychiatric disorders. Since its approval by the FDA in 1978, VPA is primarily used as a standalone or adjunctive therapy in treating various seizure types in both adult and pediatric patients, and has been recently repurposed for conditions such as bipolar disorder, diabetic peripheral neuropathy, postherpetic neuralgia, and migraine prophylaxis.^10^ Although its mode of action is multifactorial, recent studies have established VPA as a direct antagonist of histone deacetylases (HDAC), a class of epigenetic “erasers” that modulate gene expression through histone acetylation when given in higher doses. We have demonstrated that VPA is a non‐selective histone deacetylase inhibitor (HDACi) that can rapidly and reversibly increase the acetylation of nuclear and cytoplasmic proteins.^11^ Given the profound role of the histone epigenetic machinery in TBI pathogenesis and progression, the process of acetylation provides an attractive therapeutic target for the attenuation of brain injury because it is rapid, reversible, and modifiable^12^ (Figure 1).

**FIGURE 1 trf70029-fig-0001:**
[figure not shown]
Proposed mechanism of traumatic brain injury (TBI) attenuation by valproic acid (VPA) based on murine and swine studies. As a histone deacetylase inhibitor (HDACi), VPA confers numerous neuroprotective effects by preventing the deacetylation of key nuclear and cytoplasmic proteins involved in cell survival and anti‐inflammatory pathways. (A) VPA has been shown to help maintain the integrity of the blood–brain barrier (BBB) following TBI, protecting neural parenchyma and curtailing edema. (B) VPA downregulates pro‐inflammatory mediators and cytokines, mitigating neuroinflammation. (C) VPA reduces presynaptic glutamate release and enhances GABAergic transmission to diminish excitotoxicity.

In numerous studies across several animal models, we have shown that a single dose of VPA can improve survival and mitigate organ damage in models of lethal hemorrhage,^13^ poly‐trauma,^14^, ^15^ septic shock,^16^ ischemia‐reperfusion,^17^ and TBI.^18^ We first tested the protective role of VPA (300 mg/kg) following hemorrhagic shock in rat models subjected to 60% blood‐volume loss. There, we found that VPA boasted a survival rate of 75% compared to 25% in the control group.^13^

When we tested the neuroprotective effects of VPA alone for TBI in swine models, we found that a single dose of VPA (150 mg/kg) significantly improved survival in lethal TBI injury (83%) compared to animals that were resuscitated with normal saline (17%).^15^ Additionally, post‐TBI VPA treatment significantly ameliorated brain lesions, neuroinflammation, and edema while circulating levels of TBI biomarkers (e.g., GFAP) were also diminished.^18^, ^19^ Given that TBI and hemorrhagic shock frequently present simultaneously, we conducted experiments to determine the neuroprotective effect of VPA in combined TBI and hemorrhagic shock in a swine model. In this set of experiments, swine were subjected to controlled TBI and 40% estimated total blood volume loss. In this combined TBI and hemorrhagic shock model, animals that were treated with standard resuscitation augmented with VPA demonstrated significantly quicker neurological recovery, increased cognitive function, and smaller brain lesion sizes at POD 3 and POD 10 compared to the standard resuscitation group.^20^ In another experiment testing the effect of VPA on hemorrhagic shock, we demonstrated that animals subjected to lethal hemorrhage (50% estimated blood volume) had significantly better outcomes when treated with VPA and standard damage control resuscitation (DCR) protocol (80% survival) versus DCR alone (20% survival).^21^

We also tested VPA in a model of simulated PFC where blood transfusion was delayed for 72 h, and showed that animals treated with VPA required significantly less crystalloid resuscitation, had fewer post‐operative neurological impairments, and had a smaller brain lesion size compared to controls.^21^, ^22^

In addition to immediate neuroprotection, VPA has also been shown to enhance long‐term healing of the injured brain as seen by decreased neural apoptosis, inflammation, and degenerative changes, and improved neural plasticity 30 days post‐TBI.^23^ Pharmacokinetic (PK) data from our dose‐escalation trial show that the concentration of free VPA at the end of infusion strongly correlates with Neurological Severity Score (NSS), with doses as low as 50 mg/kg conferring neuroprotective effects.^24^ We anticipate that PK data obtained during our upcoming clinical trial can be used to further fine‐tune the optimal dosing regimen for use in trauma patients.^24^ In summary, across our numerous experiments studying the neuroprotective effects of VPA in animal models, it has become increasingly evident that VPA has the potential to be an effective and safe therapy for TBI in trauma patients.

## DOSE CONSIDERATIONS

3

Typical VPA dosing as an anti‐seizure agent ranges between 15 and 60 mg/kg/day. However, animal studies show that much higher doses (100–300 mg/kg) are needed in the setting of lethal hemorrhage to improve survival. To determine the lowest VPA dose that would offer a survival benefit following lethal injury, we completed a dose‐escalation study in a model of lethal polytrauma, hemorrhagic shock, and traumatic brain injury in swine.^15^ There, we discovered that VPA administered as a single IV dose of 150 mg/kg over 3 h significantly improved survival (83% vs. 17% in control; *p* < .05) and induced protective changes in the proteome that mediate cellular ischemia and inflammation. Follow‐up studies in non‐lethal injury models, however, suggest that a lower dose of 50 mg/kg may confer a similar level of neuroprotection as 150 mg/kg.^24^ To ensure the safety of higher doses of VPA in humans, we performed a double‐blind, placebo‐controlled Phase I clinical trial,^25^ where escalating doses of VPA were administered over 60 min via intravenous infusion in 59 healthy human subjects starting at 15 mg/kg and going up to 140 mg/kg (Figure 2). Subjects reported mild adverse effects (AEs)—including hypoacusis, chills, headache, tinnitus, and nausea—which were not different between the three highest dose cohorts (120, 130, and 140 mg/kg), and resolved within 12 h of infusion. Given that our proposed doses for this clinical trial will be less than these AE‐inducing doses (i.e., 50 and 100 mg/kg as described below), these findings suggest that the potentially beneficial effects of VPA significantly outweigh the mild side effects in the setting of severe injuries. Further, since our clinical trial requires only a single dose of VPA, dose‐limiting toxicities (DLTs) associated with long‐term VPA administration (or multiple doses) are not relevant.^27^, ^28^ Like most drugs, the circulating levels of VPA are also affected by body mass and surface area, and animal data must be converted into human dose equivalents.^29^ When we tested the serum levels of VPA in humans who had received doses ranging between 60 and 120 mg/kg, we found them comparable to levels in swine that were given doses as high as 300–400 mg/kg. Analyzing the human and swine dosing data together suggests that a swine dose of 100–150 mg/kg may be equivalent to a calculated human dose of 60–90 mg/kg. Therefore, we are proposing to test two doses of VPA: a lower (50 mg/kg) and a higher dose (100 mg/kg) of VPA against the standard of care.

**FIGURE 2 trf70029-fig-0002:**
[figure not shown]
Plasma VPA levels over time in different dose cohorts (*n* = 6 per cohort, except the 150 mg/kg group, which had two subjects).^26^

## VALPROIC ACID FOR TRAUMATIC BRAIN INJURY TRIAL (VIBRANT) CLINICAL TRIAL

4

The objective of this trial is to determine the efficacy of the administration of two different VPA doses in the acute setting in patients who have experienced moderate to severe TBI. We hypothesize that early administration of VPA will result in better neurological outcomes and long‐term recovery. While the exact mechanism behind VPA's neuroprotective effects in TBI patients remains unknown, there is adequate evidence supporting VPA's cytoprotective effects in the acute trauma setting to justify a phase 2/3 clinical trial. We received FDA approval (IND# 146723) for a randomized, double‐blinded, placebo‐controlled, multicenter superiority trial to evaluate the efficacy, safety, tolerability, pharmacokinetics, and pharmacodynamics of VPA in subjects with moderate to severe traumatic brain injury due to blunt trauma, which we have short‐named the **V**alproic Ac**I**d for Traumatic **BRA**in I**N**jury **T**rial (VIBRANT). This phase 2/3 clinical trial will be conducted across nine academic level 1 trauma centers across the United States, and is designed to evaluate the safety and efficacy of early administration of VPA in patients with moderate (Glasgow coma scale [GCS] 9–12) to severe (GCS 3–8) TBI relative to the current standard of care.

Enrolled patients with moderate to severe TBI as rated on the Glasgow Coma Scale between 3 and 12 due to blunt trauma will be randomized to the control arm, where they will receive standard‐of‐care treatment as defined in the Brain Trauma Foundation Guidelines in addition to a normal saline (250 mL 0.9% sodium chloride solution) vehicle, or the experimental arm where they will receive standard of care treatment and a single intravenous administration of VPA (Depacon®) at a dose of either 50 mg/kg (low‐dose VPA group) or 100 mg/kg (high‐dose VPA group) infused over 1 h.^8^ Treatment will be started within 120 min of the onset of the injury, and infusion will begin as soon as TBI is confirmed on the CT scan. All supportive care, imaging studies, and surgical interventions will adhere to the best clinical care guidelines.^8^, ^30^ Patients enrolled in the control arm will receive a 250 mL 0.9% sodium chloride solution injection that will be prepared similarly to, and visually resemble the study drug. Additionally, the saline control will be administered identically to VPA in the experimental arm. The purpose of including placebo‐treated subjects is to ascertain whether any abnormalities observed are due to VPA or environmental conditions and study procedures.

Given that this trial's intervention—a single dose of VPA (50 or 100 mg/kg) administered over 1 h—is completed once at the time of initial treatment, discontinuation of intervention does not apply to our trial. Following the single administration of VPA, there will be no ongoing or repeated interventions unique to the experimental arms; all subsequent interventions will follow standard TBI and resuscitation management protocols and will be provided equally to all enrolled patients at the discretion of the attending physician. If four patients experience adverse or serious events following VPA administration that are probably or definitely related to the study intervention, a potential trial enrollment pause will take place to perform a safety review. Investigators must use caution when administering concomitant therapies (Table S1), as VPA exhibits well‐known and defined drug interactions with several classes of therapeutics. Notably, due to hepatic clearance of VPA, drug–drug interactions may likely become less important over the course of hospitalization and should be considered by participating physicians and pharmacists. The administration of VPA is independent of posttraumatic seizure prophylaxis or treatment, and other adjuncts should be used for this purpose if desired or necessary. Past studies exploring VPA's use in the context of posttraumatic seizure mitigation were inferior compared to phenytoin.^31^ This trial does not have any provisions for ancillary or post‐trial care to enrolled patients.

The primary endpoint in this study will be the GOS‐E at 3 months post‐injury. Secondary endpoints include hemorrhagic progression of the contusion (HPC) (as measured by follow‐up CT scan over the first 24 h post‐injury), and Disability Rating Score (DRS) at discharge and at 3 months post‐injury. Exploratory endpoints will include 6‐month DRS and GOS‐E, as well as GCS 24 h post‐injury. In addition, we will monitor PK and pharmacodynamic (PD) data of VPA in the injured patient population as well as coagulation parameters including Prothrombin Time (PT), Activated Partial Thromboplastin Time (aPTT), International Normalized Ratio (INR), as well as Thromboelastography (whenever available). Endothelial markers including serum syndecan‐1, E‐selectin, and Intercellular adhesion molecule [ICAM]‐1 will be measured as well. Sub‐stratification of TBI severity into moderate (GCS 9–12) and severe (GCS 3–8) categories will also be assessed as exploratory endpoints (Table S2). The timing of patient enrollment is depicted in Figure 3.

**FIGURE 3 trf70029-fig-0003:**
[figure not shown]
Study schematic for the VIBRANT trial.

The secondary outcomes can all be treated as continuous variables and will therefore be analyzed using linear regression models. The structure of the analysis will be similar to that of the primary outcome. Specifically, for each secondary endpoint, a linear regression model will be fit with that endpoint as the response variable, with treatment group as the primary predictor of interest, with site and TBI severity as additional covariates. To determine if this endpoint differs between any pair of the three treatment groups, a second model will be fit without treatment group as a predictor and compared to the first model using a likelihood ratio test. If the test is significant at α = 0.05, each pair of treatment contrasts (3 total: control vs. 50 mg, control vs. 100 mg, 50 vs. 100 mg) will be tested separately for differences in the given secondary endpoint. The linear regression models will be fit using the lm function in R. As with the primary endpoint, the secondary endpoints will be analyzed according to the ITT principle, with an as‐treated sensitivity analysis.

Exploratory endpoints will be analyzed using the same ordinal logistic or linear regression modeling techniques as described for primary and secondary endpoints, depending on the nature of the outcome. In addition, for binary outcomes, logistic regression modeling will be performed. Multiple imputation as implemented in the MICE (Multiple Imputation by Chained Equations) R package will be used for missing data. All variables included in the analyses of the primary and secondary endpoints will be included in the imputation models: 3‐month GOS‐E, hemorrhagic progression of the contusion, disability rating score (DRS) at discharge, 3‐month DRS, treatment group, TBI status, site, and numerous other variables outlined in the protocol. Ten imputed datasets will be generated, and results will be pooled according to Rubin's rules for both primary and secondary outcomes. To account for the possibility that missingness is related to the outcome, we will perform numerous sensitivity analyses to determine the robustness of our findings to non‐random missingness, outlined in detail in the trial protocol.

To guard against the possibility of continuing the trial if there is no benefit to the treatment, we plan to conduct an interim futility analysis when follow‐up is complete for *n* = 150 participants. If the conditional power estimate falls below 20%, trial continuation will be reassessed for futility. Conditional power will be calculated under the observed outcome distribution for these *n* = 150, as well as the three assumed scenarios examined (Table S4). The potential stopping of the trial will be discussed with the Data Safety Monitoring Board (DSMB) and regulatory consultants. The study includes no pre‐specified rules for stopping the trial early for efficacy, and all interim analyses are limited to safety monitoring.

## RECRUITMENT

6

In 1996, the FDA created the exception from informed consent (EFIC) pathway for trials conducted on incapacitated individuals with life‐threatening conditions in which the time‐window needed for treatment is too narrow to obtain consent from the patient's surrogate before treatment.^33^ This trial will utilize the EFIC pathway given the time‐sensitive nature of administering VPA in TBI patients. Given that (i) patients will have an altered mental status secondary to TBI and thus be unable to provide consent before study enrollment and (ii) legally authorized representatives (LARs) are often not immediately available at the injury scene, sufficient justification exists for an exception from informed consent to administer (and study) an intervention that may have significant outcome benefits to this patient population. A past TBI trial (RAMPART) employing the EFIC pathway reported that the vast majority (83%) of subjects had positive views of enrollment, and were glad that they or their family members were enrolled in the EFIC trial; this trial will serve as a template for our study.^34^

At each participating center, a dedicated study team member will be available to obtain informed consent from patients or their LARs prior to enrollment, when it is feasible. If a patient is unable to give consent, no LAR is available, there is no evidence the patient has opted out of participation as a result of community consultation, and the patient meets all requisite eligibility criteria, they will be enrolled in our study. In this circumstance, a designated member of the research team will make frequent attempts as soon as feasible to contact a LAR or family member to provide information about the study and allow them the opportunity to make decisions regarding the patient's continued participation. In addition to consent protocols for patient enrollment, consent will be requested for follow‐up after hospital discharge to coordinate 3‐ and 6‐month post‐infusion follow‐up visits.

At each participating site, the pharmacy will prepare single‐unit dose bags for IV administration, which will be labeled with blinded study information including study number, subject number, and randomization assignment by a member of the dedicated study team at the participating site. The bags will be visually indistinguishable from each other, and the study team members will be blinded to the group allocation. Each participating site will employ the centralized, online, REDCap Electronic Data Capture System to determine the allocation of newly enrolled patients and label placebo or study drug IV preparations with blinded study information accordingly. Each study participant will be assigned a unique identification code that is de‐identified and specific to the site they were treated at, e.g. 01‐001 for patient one at site one, 02‐001 for patient one at site two, etc. The key to participant identification codes will be available to the study team and principal investigators and safeguarded as outlined in the study protocol. All of the trial data will be housed on central servers, protected and encrypted per Northwestern University policy and the study protocol.

Given that blinding occurs at the level of drug preparation by the participating site's dedicated study team, all trial participants, investigators, care providers, outcome assessors, and data analysts will be blinded. Available identifiers will include blinded study information, including study number, unique subject number, and randomization assignment. Investigators will have access to a sealed electronic envelope for enrolled patients under their care, to be opened in the event that knowledge of the administered substance becomes necessary for adequate patient care. Should the electronic envelope be accessed and unblinding occur, the date of opening and reason for opening will be recorded in the file.

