NUDACC under the leadership of [name] will act as the data coordinating center to provide the data management, storage, and analytical support. NUDACC (https://www.feinberg.northwestern.edu/sites/nudacc/index.html) has the expertise to provide the full spectrum of services and support that is needed for high‐quality translational and clinical research. NUDACC supports the investigators, but administratively [name] reports to the Associate Vice President of Research/Senior Associate Dean for Clinical and Translational Research. All study data will be subjected to weekly quality assurance reviews including range, logic, and consistency checks. Data queries will be administered and monitored for resolution in collaboration with the study project manager. Experienced biostatisticians at NUDACC will analyze the data to ensure quality and completeness and generate the required reports. In addition, Broom Street Associates will provide regulatory and monitoring expertise for this project. The timely evaluation of ongoing and cumulative data allows early identification of site and study‐specific problem areas that warrant immediate remediation. Study monitoring reports will include data such as: actual versus expected study enrollment; demographic characteristics of participants by protocol‐driven parameters; enrollment status of participants (active, discontinued, loss to follow‐up, etc.); adverse events (AEs) by severity; details about participants experiencing SAEs, including SAEs resulting in death; clinical and laboratory results; and more. The NUDACC team will provide confidential reports for the DSMB, and separate (blinded) reports for the investigators. DSMB will provide independent oversight as described above.

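### The protocol contradicts itself on who holds the allocation at the site: the study team handles labelling and, in one place, preparation, yet is declared blinded, and no unblinded role is named

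*Protocol article*

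**What the plan says.** All the blinding mechanics are in the Recruitment section (section 6) of the protocol article.

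- **Preparation, first statement:** "At each participating site, the pharmacy will prepare" the single-dose bags.
- **Labelling:** the bags are "labeled with blinded study information including study number, subject number, and randomization assignment by a member of the dedicated study team" at the site.
- **Blinding of that group:** the next sentence says that the bags look alike and "the study team members will be blinded to the group allocation". It makes no exception for whoever does the labelling.
- **Access to the allocation:** each site uses REDCap to find the allocation of a new patient and to "label placebo or study drug IV preparations with blinded study information accordingly". The text does not say which person at the site does this.
- **Preparation, second statement:** the next paragraph starts from the premise that "blinding occurs at the level of drug preparation by the participating site's dedicated study team". It concludes that participants, investigators, care providers, "outcome assessors, and data analysts will be blinded".
- **Identifiers:** directly after that, "Available identifiers will include blinded study information, including study number, unique subject number, and randomization assignment".
- **Unblinding:** a sealed electronic envelope may be opened if patient care requires it, with date and reason recorded.

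The Oversight and Monitoring section (section 8) adds two relevant facts. Site principal investigators train and certify their own study team members, who gather the data, and the principal investigators score patients independently to check interrater agreement. The site pharmacy is monitored for, among other things, correct labelling.

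**The concern.** Someone at each site must know whether a given patient gets saline, 50 mg/kg or 100 mg/kg in order to make up the bag. A double-blind trial names that person and keeps the role apart from care and outcome assessment. Here the tasks that need the allocation, or that display it, fall at least partly to the dedicated study team, which the same section declares blinded.

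The primary endpoint is the 3-month GOS-E, and the DRS at discharge and at 3 months is a secondary endpoint. Both depend on a rater's judgement. The judgement of whether an adverse event is related to treatment also matters, because four related events can trigger an enrolment pause. A rater or investigator who knows the arm can shift these judgements without intending to. No analysis can undo that afterwards.

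**Working it through.** The plan gives no figure on this point, so the check is a comparison of statements. Two questions decide it: what the term *randomization assignment* on the label means, and who makes up the bag.

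**1. The term means the treatment arm.** Then anyone who reads the label learns the arm. The labelling statement and the statement that study team members are blinded contradict each other directly. The identifier list repeats the problem immediately after the list of blinded roles.

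**2. The term means a code.** Then the label conceals the arm, but the bag still has to contain the right product. There are two cases:

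- *The study team prepares the drug* (second statement on preparation). At least one team member knows the arm. This contradicts the unqualified statement that team members are blinded.
- *The pharmacy prepares the drug* (first statement). The team can stay blinded, but only if REDCap shows the allocation to the pharmacy alone and the team member who attaches the label sees no more than the code. The text states neither condition. It says only that the site finds the allocation and labels to match.

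**3. Result.** Only one combination agrees with the declared blinding: a coded label, preparation by the pharmacy only, and allocation visible to the pharmacy only. The document contradicts the second element in one sentence, leaves the third unstated, and names the label content in a way that obscures the first. Labelling is also unsettled. The Recruitment section gives it to a study team member, while the Oversight and Monitoring section monitors the pharmacy for it.

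**4. Link to the endpoint.** The Oversight and Monitoring section has trained and certified study team members gather the data, with the principal investigator scoring as a check. The labeller and the raters therefore come from the same site group, and no separation between them is stated. This is an inference about the group. The document does not say that the person who labels a bag later scores that patient.

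**The case against.** The strongest reply is that a coded label was plainly intended. The label content is twice called blinded information, the bags look alike, and a logged electronic envelope would be pointless if the label named the arm. This largely stands, and it rules out the conclusion that the blind will fail. It does not answer who sees the allocation in REDCap or why preparation is given to two different groups.

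A second reply is that a journal article condenses the full protocol, so detail may be found there. That would answer a complaint that something is missing. Here the article states the mechanics positively and its statements conflict.

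Three stronger readings are tempting and are not supported:

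- **A shared arm code.** A reader might infer that one emergency unblinding would reveal every patient carrying the same code. The documents describe no code shared between patients. They mention a unique subject number and envelopes for enrolled patients.
- **A conflict over blinded analysts.** A reader might infer one because "The NUDACC team will provide confidential reports for the DSMB, and separate (blinded) reports for the investigators". A separate unblinded statistician would resolve it. The section leaves statistician support and reporting for the monitoring board to a charter that is still to be written, which is a normal place for that detail.
- **A stated inflation of type I error.** A reader might assume a rating shift and compute one. The documents give no size or frequency of leakage. A figure for a single ungated comparison would also misdescribe the plan, because the Statistical Methods section tests pairwise contrasts only after a significant three-group likelihood ratio test.

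**Conclusion.** The concern holds as an internal contradiction in the written blinding procedure. The statements on labelling, access to the allocation and preparation cannot all be reconciled with the statement that study team members, investigators and outcome assessors are blinded, and no unblinded role is named. It applies at all nine sites and to every patient, because it concerns the standard procedure for each bag.

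It does not show that the blind will be broken. The probable intent is a coded label, and a site working to that intent with pharmacy-only access would be properly blinded. The size of any bias cannot be stated from the documents. The importance rests on two points. The primary endpoint is scored by raters drawn from the group that the text allows to hold the allocation, and a blind lost during enrolment cannot be restored. The conclusion assumes that the section is read as written and that the full protocol does not already say otherwise. If it does, the article and the protocol should be brought into line.

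**What to change.** 1. State that the site pharmacist, who belongs neither to the study team nor to the raters, is the only site role that sees the allocation in REDCap and that prepares and labels the bags. The logged emergency envelope remains the one exception.
2. Reconcile the two statements on who prepares the drug, and the statements on who labels it, so that all name the pharmacist.
3. Replace the randomization assignment, on the label and in the list of available identifiers, with a unique, non-informative kit number.
4. State that outcome assessors have no access to the allocation.

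The cost is protocol and pharmacy instructions plus one REDCap permission, provided the first statement on preparation describes actual practice. If any site had planned for its study team to prepare the drug, that site must move the task to the pharmacy and check that cover is available within the treatment window. No change to sample size, endpoint or analysis is needed. It should be done before enrolment starts.
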